### Sample size calculation and statistical considerations

Based on the current literature our hypothesis is that 10 % of the treated tumors will recur after the initial treatment (primary technique efficacy 90 %), which implies a local recurrence rate of 0.1 [5, 30]. Choosing a target width of 0.25 with p ≤ 0.05, we used the confidence interval formula “Exact” for two-sided confidence intervals for one proportion (Clopper-Pearson) [31, 32]. With this formula, actual width is 0.249, with a 95 % confidence interval of 0.020–0.269. This calculation results in a sample size of 29 patients. Considering a 5 % loss to follow-up, the total number of patients needed is 31.

All clinicopathological and procedural variables will be described and analyzed. Continuous variables will be summarized with standard descriptive statistics including means, standard deviations, medians and ranges. Categorical variables will be summarized with frequencies. *P*-values ≤ 0.05 will be considered statistically significant. Univariate survival analysis will be performed using the Kaplan-Meier method. Differences in local recurrence rate between subgroups like tumor size and adjuvant chemotherapy will be analyzed descriptively since the expected number of recurrences is too small for statistical analysis.

The accuracy of ^18^F-FDG PET-CT and 4-phase liver CT in diagnosing local recurrences will be investigated by comparison to the reference standard. Interobserver-variability will be determined using Cohen’s Kappa. Sensitivity and specificity of both techniques will be calculated with their respective 95 % confidence intervals. McNemar’s test is used to assess a statistically significant difference between both imaging modalities.

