### Imaging follow-up

The main concern following tumor ablation is the risk of developing LTP. Early diagnosis of LTP is imperative because repeated treatment can still effectuate complete tumor clearance, especially for smaller recurrences. CeCT is the current mainstay of staging and follow-up [39]. One shortcoming of ceCT in the monitoring of post-ablative lesions for recurrent disease is the presence of post-ablation effects. Because reactive tissue and viable tumor can both present as hypodensity around the ablated lesion, their distinction can be difficult [24]. Due to the visualization of increased glucose metabolism in tumor cells, ^18^F-FDG PET has proven a very sensitive and accurate tool for the diagnosis of tumor manifestations in patients with colorectal carcinoma [39]. Using ^18^F-FDG PET-CT, ^18^F-FDG PET images are combined with CT in a single session. Anatomical and morphological information from CT is used to increase the precision of localization, extent, and characterization of lesions detected by ^18^F-FDG PET [21]. Several studies have shown the superiority of ^18^F-FDG PET-CT over morphologic imaging alone in the follow-up after ablation of CRLM: sensitivity and specificity for the detection of LTP are 92 % 100 % for ^18^F-FDG PET-CT compared to 83 % and 100 % for ceCT [24]. However, the diagnostic accuracy of ^18^F-FDG PET and ^18^F-FDG PET-CT is strongly affected by chemotherapy, so for patients receiving chemotherapy during follow-up after IRE ceCT may prove the most reliable imaging modality.

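### At the roughly 3 recurrences the plan expects, McNemar's test cannot reach p ≤ 0.05 on sensitivity, and the plan does not say which accuracy measure the test addresses

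*Protocol article*

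**What the plan says.** All the planning statements are in the Protocol article, section Sample size calculation and statistical considerations.

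- Expected recurrence: "10 % of the treated tumors will recur after the initial treatment".
- Size: the trial is sized only for the width of a confidence interval around that rate. "This calculation results in a sample size of 29 patients", and "Considering a 5 % loss to follow-up, the total number of patients needed is 31".
- Significance threshold: p-values "≤ 0.05 will be considered statistically significant".
- Subgroup differences in recurrence are to be described, not tested, "since the expected number of recurrences is too small for statistical analysis".
- Imaging accuracy: sensitivity and specificity of PET-CT and 4-phase CT are each to be given with a 95% confidence interval. McNemar's "test is used to assess a statistically significant difference between both imaging modalities". Neither the accuracy measure tested nor the form of the test (exact, mid-p, corrected or uncorrected) is named.

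In the Discussion, under Imaging follow-up, the article reports from earlier work that "sensitivity and specificity for the detection of LTP are" 92% and 100% for PET-CT, against 83% and 100% for contrast-enhanced CT.

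**The concern.** Sensitivity is estimated only in lesions that recur. The plan expects about three of these and says itself that such a number does not support statistical analysis of subgroups. In the next paragraph it plans a significance test between the two modalities, and the sensitivity part of that test depends on the same three lesions.

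Two things are at stake. If the test is applied to sensitivity, a non-significant result at the expected count says nothing about the modalities, yet it could be read as showing that they detect recurrence equally well. If it is applied to all lesions together, about nine in ten contribute through false positives, so a p-value that looks like a verdict on detecting recurrence would mostly be a verdict on specificity. Accuracy is a named secondary endpoint, and the article lists follow-up guidelines among the things the trial aims to inform.

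**Working it through.** **Inputs.** Recurrence rate 0.10, 29 evaluable and 31 in total, threshold 0.05 (sample size section); sensitivities 0.92 and 0.83 (Discussion, Imaging follow-up). Assumptions: McNemar's test is two-sided, as is usual (the article states two-sidedness only "for two-sided confidence intervals for one proportion (Clopper-Pearson" interval), and there is one target lesion per patient unless stated otherwise.

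**1. The plan's own figure.** Clopper-Pearson limits with x = 0.1n: n = 28 gives width 0.2535; n = 29 gives 0.0203 to 0.2691, width 0.2487. So 29 is the smallest n with width at most 0.25, and 29/0.95 = 30.5, rounded up to 31. The stated size is reproduced. It contains no allowance for comparing modalities.

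**2. Expected recurrences.** 29 × 0.10 = 2.9; 31 × 0.10 = 3.1. About 26 of 29 lesions are recurrence-free.

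**3. Smallest attainable p on sensitivity.** The extreme case is that one modality finds all m recurrences and the other finds none. Then exact p = 2 × 0.5^m; mid-p = 0.5^m; the uncorrected chi-square statistic is m and the corrected one is (m − 1)²/m, each on 1 df.

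| m | exact | mid-p | uncorrected | corrected |
|---|---|---|---|---|
| 3 | 0.25 | 0.125 | 0.083 | 0.248 |
| 4 | 0.125 | 0.0625 | 0.0455 | 0.134 |
| 5 | 0.0625 | 0.031 | 0.025 | 0.074 |
| 6 | 0.031 | 0.016 | 0.014 | 0.041 |

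At m = 3 no form reaches 0.05. The minimum is 6 recurrences for the exact and corrected forms, 5 for mid-p and 4 for the uncorrected form, all discordant in one direction.

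**4. Chance that significance is possible at all.** With the number of recurrences X ~ Binomial(n, 0.10):

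- P(X ≥ 6) = 6.4% (n = 29) or 8.3% (n = 31).
- P(X ≥ 4) = 33% (n = 29) or 38% (n = 31).

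These are ceilings on power for the exact and uncorrected forms, because they require complete one-way disagreement.

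**5. Power at the cited sensitivities.**

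- Independent errors: discordant probabilities 0.92 × 0.17 = 0.156 and 0.08 × 0.83 = 0.066.
- Maximally overlapping errors (every CT detection is also a PET-CT detection): 0.92 − 0.83 = 0.09 and 0.

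Averaged over Binomial(29, 0.10), exact power is 4.4 × 10⁻⁶ (independent) and 2.1 × 10⁻⁷ (overlapping), both below 0.001%. The uncorrected test reaches about 0.1% at most.

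**6. Recurrences needed for 80% exact power.** 87 with overlapping errors (80.6%) and 227 with independent errors (80.0%), against about 3 expected.

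**7. Recurrence-free lesions.** With an assumed one-way discordance of 25% in 26 lesions, the exact test rejects when at least 6 are discordant: P(Binomial(26, 0.25) ≥ 6) = 66%. Over all 29 lesions with the same discordance it is 77%. The test can therefore be informative about specificity.

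**The case against.** **The sentence does not restrict the test to sensitivity.** This is correct, and it limits the point. A reader might infer that the McNemar comparison as a whole is bound to be non-significant; step 7 shows otherwise. Specificity is also a real question here: the article describes FDG uptake from inflammation that can last for months after the procedure, and reactive tissue that resembles tumour on CT. What remains is that an unnamed measure lets a specificity result pass for one about detecting recurrence.

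**The recurrence count is random and the rate may exceed 10%.** A reader might infer that non-significance on sensitivity follows whatever the truth is. That is strict only at the expected count. The plan's own interval reaches 26.9%, and the Background reports complete eradication in 67–100% of tumours. In 29 lesions P(X ≥ 6) is 54% at a rate of 20%, 83% at 26.9% and 95% at 33%. The rate is also per tumour while 29 counts patients: with 1.5 target lesions per patient (an assumption, about 45 lesions), P(X ≥ 6) at 10% is 29%. Significance then becomes attainable but not likely. With 8 recurrences (29 × 0.269 = 7.8), power at 92% versus 83% is below 0.1% for the exact test and below 2% for the uncorrected one.

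**An unpowered secondary test is common, and the detail may stand in a fuller document.** The absence of a power calculation is indeed no error, and the form of the test may be given elsewhere. The inconsistency is within the article's own section: it treats the expected recurrences as too few for one comparison and tests another that rests on them.

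**Intervals are already planned.** They would show the imprecision: 3 of 3 detected gives an exact 95% interval of 29% to 100%. They do not give the paired difference. Nothing in the article says that non-significance will be taken as equivalence, so the misreading is a risk and not a stated intention.

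**Conclusion.** The point holds for sensitivity at the recurrence count the plan expects. With 3 recurrences every two-sided form of McNemar's test has a smallest possible p above 0.05. The 6.4% ceiling belongs to the exact test with n = 29 and a 10% rate, and must not be quoted as a general maximum; the uncorrected test has a ceiling of 33% under the same conditions. The power figures rest on the cited sensitivities and span independent to maximally overlapping errors. The point does not extend to specificity or to the test as a whole. It is a moderate matter of reporting on a secondary endpoint, and it leaves the primary efficacy estimate and the sample size untouched.

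**What to change.** 1. Declare the comparison of sensitivity descriptive, for the reason the section already gives for subgroups.
2. Next to the intervals already planned, report the paired 2×2 table of the two modalities in recurrent lesions, and the paired difference in sensitivity with a confidence interval suited to small paired samples.
3. If a test is kept, apply exact McNemar to specificity in recurrence-free lesions and label it as such. Do not report one p-value pooled over all lesions as a comparison of detection.
4. State that a non-significant result is not evidence of equal accuracy.

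The change is to wording and tables only; no further patients, scans or readings are needed. The cost is a sensitivity p-value that could not be informative at the expected number of recurrences. If recurrences turn out to be far more frequent than planned, a test that could then in principle reject is also given up, but at the cited sensitivities its power would still be very small.

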## Discussion

### IRE for colorectal liver metastases

New cancer treatments are typically best defined from phase III randomized trials comparing the investigated therapy with the current standard. However, in the field of local tumor ablation, this has proven a difficult challenge. Since its introduction decades ago, the number of randomized trials remains limited. An attempt to organize a trial comparing RFA to surgical resection has failed (French FFCD 2002–02) and it is unlikely that another trial can be organized in the near future [33]. The current literature on the clinical application of IRE is scarce with no randomized controlled trials. However, because the indication for IRE lies with tumors in which no other suitable local therapy is available, a randomized trial comparing IRE to e.g. surgical resection or thermal ablation is not unrealistic at this point in time.

Results of single-arm studies on hepatic IRE report a high variation in efficacy, with local recurrence rates between 67–100 % [17]. Similar to RFA, efficacy is higher for tumors ≤ 3 cm. However, since IRE is only used as a ‘last resort’ curative treatment option in patients that would otherwise receive palliative chemotherapy, these early efficacy rates are promising and encourage larger prospective studies.

### Feasibility

Intraprocedural monitoring and control of ablation play a critical role in the success of tumor ablation [34]. The feasibility of real-time monitoring with US during hepatic IRE has been demonstrated in both animal and human studies. The ablation zone immediately appears as a hypoechoic area with well-defined margins [16, 35, 36]. Immediate postprocedure ceCT also shows a well-defined hypodense area on the portal venous phase with variable periablational hyperenhancement [37, 38]. The size and shape of the IRE ablation zone on both US and CT has proven to correlate reliably with the pathologically defined zone of cell death [36, 37]. These imaging modalities could therefore be used to ensure that the realm of ablation encompasses the originally targeted volume with a sufficient margin [15], which is a focus of the presented trial.

### Imaging follow-up

The main concern following tumor ablation is the risk of developing LTP. Early diagnosis of LTP is imperative because repeated treatment can still effectuate complete tumor clearance, especially for smaller recurrences. CeCT is the current mainstay of staging and follow-up [39]. One shortcoming of ceCT in the monitoring of post-ablative lesions for recurrent disease is the presence of post-ablation effects. Because reactive tissue and viable tumor can both present as hypodensity around the ablated lesion, their distinction can be difficult [24]. Due to the visualization of increased glucose metabolism in tumor cells, ^18^F-FDG PET has proven a very sensitive and accurate tool for the diagnosis of tumor manifestations in patients with colorectal carcinoma [39]. Using ^18^F-FDG PET-CT, ^18^F-FDG PET images are combined with CT in a single session. Anatomical and morphological information from CT is used to increase the precision of localization, extent, and characterization of lesions detected by ^18^F-FDG PET [21]. Several studies have shown the superiority of ^18^F-FDG PET-CT over morphologic imaging alone in the follow-up after ablation of CRLM: sensitivity and specificity for the detection of LTP are 92 % 100 % for ^18^F-FDG PET-CT compared to 83 % and 100 % for ceCT [24]. However, the diagnostic accuracy of ^18^F-FDG PET and ^18^F-FDG PET-CT is strongly affected by chemotherapy, so for patients receiving chemotherapy during follow-up after IRE ceCT may prove the most reliable imaging modality.

After IRE, immediate ceCT shows a hypodense ablation zone that does not enhance post-contrast. A transient peripheral rim of contrast enhancement can be present, representing hyperemia [15]. In the months after ablation, the ablation zone slowly decreases in size and should not show uptake of contrast. PET scans show a dynamic response to the IRE ablation. Three days following IRE, an ^18^F-FDG-avid peripheral zone surrounding the ablated region appears. This initial increase in uptake at the periphery of the IRE region may be explained by an inflammatory response, increasing metabolic activity at the targeted region as the cellular debris is removed from the ablation site [15]. In our experience the inflammatory response can persist for several months, which renders evaluation of the ablation zone with ^18^F-FDG PET difficult. On the contrary, ablated lesions that show focal rather than rim-like uptake in the periphery are considered suspect for local recurrence. Because much is still unknown about the imaging characteristics of liver lesions treated with IRE, standardized follow-up regimens are lacking. The COLDFIRE-2 trial focuses on the typical imaging characteristics of electroporated CRLM over time. The gold standard for LTP is histologic confirmation. With biopsies taken from all suspicious lesions prior to re-treatment, the trial also assesses the accuracy of the pre-defined definition of LTP on PET-CT and ceCT.

A potentially curative treatment option for a group of patients that is currently offered chemotherapy with palliative intent is of major importance. IRE may prove a safe and valuable fortification in the armory of interventional oncologists treating patients with liver tumors. The aim of the COLDFIRE-2 trial is to contribute to the available evidence on IRE with respect to safety, efficacy, imaging characteristics and follow-up guidelines. The results of the proposed trial may represent an important step towards the implementation of IRE for central liver tumors in the clinical setting.

## Abbreviations

ASA: American Society of Anesthesiologists
CEA: Carcinoembryonic antigen
ceCT: Contrast-enhanced computed tomography
CRLM: Colorectal liver metastases
CTCAE: Common terminology criteria of adverse events
^18^F-FDG: ^18^F-fluorodeoxyglucose
IOUS: Intra-operative ultrasound
IRE: Irreversible electroporation
LTP: Local tumor progression
ceMRI: Contrast enhanced MRI
MWA: Microwave ablation
NYHA: New York Heart Association
PET: Positron emission tomography
RFA: Radiofrequency ablation
VAS: Visual analogue scale
